### Interventions

After group allocation, all participants will be provided with instructions about their allocated interventions (see below). All participants will receive an educational session where they will be informed about the length of time to resolution of symptoms (realistic anticipation of therapy success), importance of adhering to wearing the foot orthoses, and issues about weight control [38]. A guideline based on the EdUReP (Education, Unloading, Reloading, Prevention) model, which provides a framework for management of tendinopathy, accompanies the intervention phase [45].

Participants will receive one of the following therapies according to their random allocation:

#### Foot Orthoses Only (FOO)

Participants in this group will receive custom-made foot orthoses fabricated by the same orthopaedic technician (AR, Ortho-Team AG, Bern, Switzerland). Foot orthoses will be fabricated out of Ethylene Vinyl Acetate (EVA, shore 40) with a thickness at the base of approximately 4 mm. The foot will be cast in a three-dimensional foam box impression in the neutral position of the foot under partial weightbearing [46]. This neutral position is already a “corrected” position for patients with the mentioned pathology. The 3D foam box impression serves as the basis for implementing correcting elements in the foot orthoses via computer-aided design software (CAD). A medial longitudinal arch is provided for arch support and a bowl-shaped heel is integrated to promote rear foot stability. Finally, the foot orthoses will be fabricated out of an EVA block by means of computerised numerical control technology (CNC). A dynamic barefoot plantar pressure distribution to evaluate dynamic foot function during walking (foot progression angle, forefoot abduction and medial loading) and qualitative gait analysis will be performed to support decision making on the amount of medial arch posting [43]. A medial longitudinal arch support will increase pressure at the medial plantar surface [47, 48], which might lead to changes in afferent input triggering neuromuscular control [34]. A top layer of Alcantara will be glued on top of each orthosis (Table 1). All participants will wear the device throughout the 12-week intervention for a minimum of 80 % of weight-bearing tasks.

#### Foot Orthoses and Eccentrics (FOE)

In addition to the use of the foot orthoses described above, eccentric strengthening exercises will be prescribed in this group (concentric portions are inherent, but emphasis is put on eccentric phases). Heel lowering movements will be performed on the edge of a stair from a calf raised position. For correction of rearfoot eversion a pair of socks will be squeezed between the calcaneii below the medial malleoli (active correction of rearfoot eversion and medial longitudinal arch flattening). This exercise will be performed twice per day with three sets of 15 repetitions per day for 12 weeks. Calf raises will be performed without the squeeze of the pair of socks to reduce load in the concentric phase. The exercise is a modified eccentric version of that proposed by Yuill and MacIntire [49]. It is combined with the loading suggestions of Alfredson for the treatment of Achilles tendinopathy [50, 51]. Increasing load (e.g., additional load with back pack) will be performed throughout the intervention as suggested by Jonsson [52]. Participants will be instructed by an experienced physiotherapist. They will receive an activity booklet to record all training sessions and possible accompanying activities. All participants will wear the foot orthoses throughout the 12-week intervention for a minimum of 80 % of weight-bearing tasks.

#### Foot Orthoses Sham (FOS)

This group will receive individually customised (sham) foot orthoses out of the same material described above. The functional elements of the sham orthoses, like arch support or a bowl-shaped heel to promote rearfoot stability, are designed to assist with blinding of patients. The foot will also be cast in a three-dimensional foam box impression without “correcting” to a neutral position of the foot under partial weightbearing [46]. The sham orthoses will not receive correcting elements via computer-aided design software (CAD). The sham foot orthoses will also fabricated out of an EVA block by means of computerised numerical control (CNC) technology. Like the other orthoses, a layer out of Alcantara will be glued to the top of the sham orthoses. All participants will wear the device throughout the 12-week intervention for a minimum of 80 % of weight-bearing tasks. The participants in this group will also get an activity booklet to record possible accompanying activity.

All three groups will receive a phone call after one, four and eight weeks to check for compliance, uncertainties and questions (Fig. 1). If necessary, monitoring sessions for members of the FOE group with the physiotherapist will be organised every four weeks to control exercise execution and to implement training load adjustments [52]. Where participants experience obvious fitting problems, orthoses will be slightly modified as necessary to ensure comfort and shoe fit.

### Outcome measures

#### Foot-Function-Index (FFI)

The evaluation of therapy efficacy will be conducted with the main outcome measure, the FFI, before and after the intervention. It will be administered before the biomechanical testing on the pre/post measurements. The FFI is recognised as a valid and reliable tool [53, 54]. It is also available and valid for German language use [41]. Furthermore, it has been used already to evaluate PTTD patients with pes planovalgus associated complaints and is considered to be an excellent tool in this circumstance [14, 15]. The overall (i.e., total) FFI score will be analysed as the primary outcome measure. The subscales of the FFI in the dimensions pain, disability and activity limitation will be analysed separately as secondary outcome measures.

#### Pain-Disability-Index (PDI)

The Pain-Disability-Index (PDI), used to evaluate functional impairment, will also be administered pre- and post-intervention as a secondary outcome [43, 55]. The PDI is a seven-item inventory designed to measure the degree to which pain interferes with function across a range of seven daily life dimensions (family/home responsibilities, recreation, social activity, occupation, sexual behaviour, self-care and life support activity). Each item ranges from 0 (no interference) to 10 (total interference) resulting in a sum score of 0 to 70 [56, 57, 44]. It is considered reliable for the assessment of functional impairment and chronic diseases especially in musculoskeletal pathology [58, 59]. The validity in overuse injuries has previously been proven [43, 55].

#### Visual Analogue Scale (VAS)

A 100 mm visual analogue scale (VAS) with the endpoints “no pain” and “worst pain possible” is administered before and after the biomechanical assessment to evaluate acute pain levels. It is valid and reliable in terms of the measurement of self-reported pain intensity [60].

#### Biomechanical testing

Biomechanical testing will take place before and after the intervention. All measurements will be taken with participants barefoot in three situations (“standing”, “level walking” and “walking downstairs”). Participants will walk on an even walkway with embedded force plates (AMTI® OR6, Watertown, USA) for ground contact detection and ground reaction force measurements at a self-selected speed. Ten successful walking trials will be collected. In addition, 10 successful trials of descending from two stair steps on the embedded force plates will be collected. This functionally relevant situation is administered to enhance load on the foot structures in a functionally relevant way [61, 62].

Participants will be prepared with reflective markers at bony landmarks according to a lower body marker set (Vicon® Plug-In-Gait lower body, Oxford, UK) to capture the kinematics and kinetics of hip, knee and ankle joints. A second 4-marker set based on suggestions by Dicharry will be used to measure dynamic navicular drop [23]. A static measurement will serve as a calibration for preceding dynamic trials. The comparison with the static trial will allow calculation of changes due to the additional load application during walking and on the stairway. A 10 camera setup (Vicon Bonita, Vicon® Motion Systems Ltd., Oxford, UK) will be used with a sampling rate of 200 Hz.

At the same time, the tibialis anterior, peroneal and gastrocnemius (medial and lateral head) muscles will be prepared bilaterally for surface EMG measurements. Localisation of disposable pregelled Al/AgCl bipolar surface electrodes (Ambu®, Medicotest®, DK, type N-00-S, distance from centre to centre: 25 mm) will be carefully determined according to Winter and Yack and the SENIAM procedures [63, 64]: The longitudinal axes of the electrodes shall be in line with the presumed direction of the underlying muscle fibres. Interelectrode impedance shall be kept below 5 kOhms by means of shaving, light abrasion, degreasing and disinfecting the skin with alcohol. The EMG electrodes will be directly connected to differential pre-amplifiers and taped to the skin. The pre-amplified signals will then be transmitted via shielded cables (fixed to the leg with Velcro straps lattice bracing) to the main amplifier (PowerPack, pfitec®, Endingen, DE). Signals will be 12-bit analogue/digital-converted and stored on a personal computer. The sampling frequency will be set at 2000 Hz.

Signal data processing of kinematic data will calculate a representative mean stride cycle from the 10 collected trials per situation and condition. The kinematic outcome measures will be calculated with the manufacturer’s software Vicon Nexus® (Vicon® Motion Systems Ltd., Oxford, UK), and MatLab® (Mathworks Inc., Natick, USA) and will then be transferred to a data spreadsheet for statistical analysis.

Post-processing of EMG signals will include rectification and calculation of one average stride cycle out of 10 consecutive stride cycles. The on-off pattern of muscle activity will then be defined above a threshold of the resting signal plus two standard deviations. Above this threshold the muscle will be considered “on”. “Off” is defined after decline of the EMG signal below this threshold. “On” and “off” will be determined automatically by customised software (LabView®-based: Software Imago, pfitec®, Endingen, DE) and checked visually by a person experienced in EMG data processing but blinded to group assignment of the individual trial. This is considered to be a reasonable procedure securing both high standardisation and validity [65]. Total time of activation (Ttot) will then be calculated as a percentage of total stride time. The onset of activation (Tini) and the time of maximum activation (Tmax) will be extracted and expressed in relation to touchdown in % of stride [66, 34, 33, 35]. Amplitudes in the gait cycle phases pre-activation (Apre), weight acceptance (Awa), midstance (Ams) and push-off (Apo) will be calculated according to the phase definition by Winter [67]: Pre-activation is defined as the period from onset of electromyographic activity (see above) to initial touchdown. Weight acceptance is the period of time between initial contact and the following 15 % of the stride period (‘early stance’). Midstance is the period from 15 % to 40 % of stride. Push-off is the period of time late in stance from 40 % of stride to toe-off [67]. The mean amplitude voltage (MAV) per gait cycle phase will be extracted and normalised to the MAV of the entire stride cycle. Hence, Apre, Awa, Ams and Apo are determined relative to the average activity and expressed as a fraction of the average amplitude (=1.0). Data will then be transferred from LabVIEW®-format to a data spreadsheet for plausibility control and statistical analysis.

Signal processing personnel will be blinded to experimental condition. The electronic database will then be checked for plausibility. All measures will be checked by range checks to estimate validity of retrieved quantities. Apparent discordant values will be tracked back to their origin and data analysis will be repeated. The data spreadsheet of all manually collected data like anthropometrics will be printed as a hardcopy. Missing values will be marked, cross-checked, added or corrected if applicable. Random re-evaluation of original data will serve for cross-checking of originally analysed biomechanical data. All outcomes and quantities of kinematic and electromyographic measurements are shown in Table 1 (primary, secondary and tertiary outcome measures).

**Table 1 Tab1:** Outcome measures

Primary outcome measure	Unit
• Foot Function Index (FFI) – total score	sum score [0–230]
Secondary outcome measures	Unit
• Foot Function Index (FFI) – subcategory pain	sum score [0–90]
• Foot Function Index (FFI) – subcategory disability	sum score [0–90]
• Foot Function Index (FFI) – subcategory activity limitation	sum score [0–50]
Tertiary outcome measures	Unit
Additional assessment of functional impairment and current pain perception	
• Pain Disability Index	Sum score [0–70]
• Visual Analog Scale (VAS) assessing pain (pre-post biomechanical testing)	Score [0–10]
Tertiary outcome measures from biomechanical data	Unit
Kinematic data from 3D movement analysis	
Distance	
• Dynamic navicular drop	Millimeter [mm]
Kinematic data from 3D movement analysis	
Angular data: angle at initial contact, maximal manifestation during stance, range	
• Foot Progression Angle	Angular degree [°]
• Forefoot to rearfoot dorsiflexion	Angular degree [°]
• Forefoot to rearfoot adduction	Angular degree [°]
• Forefoot to rearfoot supination	Angular degree [°]
• Ankle dorsiflexion	Angular degree [°]
• Ankle adduction	Angular degree [°]
• Ankle eversion	Angular degree [°]
(hindfoot with respect to tibia)	
• Ankle dorsiflexion	Angular degree [°]
• Ankle adduction	Angular degree [°]
• Ankle eversion	Angular degree [°]
(hindfoot with respect to lab)	
• Knee flexion	Angular degree [°]
• Knee adduction	Angular degree [°]
• Knee internal rotation	Angular degree [°]
• Hip flexion	Angular degree [°]
• Hip adduction	Angular degree [°]
• Hip internal rotation	Angular degree [°]
Neuromuscular activity	
EMG of M. tibialis anterior, M. peroneus longus, M. gastrocnemius lateralis/medialis, M. soleus	
• Onset of activation	% of stride
• Time of maximum activation	% of stride
• Total time of activation	% of stride
• Normalized amplitude in preactivation	arbitrary unit [uV/uV]
• Normalized amplitude in weight acceptance	arbitrary unit [uV/uV]
• Normalized amplitude in mid-stance	arbitrary unit [uV/uV]
• Normalized amplitude in push-off	arbitrary unit [uV/uV]

Primary, secondary and tertiary outcome measures of this RCT

### Data analysis

Data will be transferred from Case Report Forms to Microsoft® Excel for Windows (current version) spread sheets and later processed by SPSS® (current version). Biomechanical data will be processed with the outlined software and final quantities will also be transferred to spreadsheets for statistical analysis.

Statistical analysis will be performed descriptively after plausibility control. First, testing of normal distribution (Shapiro-Wilk test) of data will be followed by the calculation of mean, standard deviation and 95 % confidence interval. Primary outcome measure (FFI total score) at measurement points 0, week 6 and week 12 will be analysed by 3x3 Analysis of Variance (ANOVA) with repeated measures identifying differences in the FFI across groups (FOO, FOE, FOS) and test sessions. This also applies for the secondary outcome measures (FFI pain subcategory, FFI disability subcategory and FFI activity limitation subcategory). The primary endpoint will be set at 12 weeks. Biomechanical data will be analysed descriptively. Pre-post comparisons of those tertiary outcome measures will also be performed where indicated after descriptive analysis by 2×2 repeated measures ANOVA (factor group and test day).

Sample size calculation has been based on the outlined protocol with three intervention groups and the same primary outcome as Kulig et al. [14, 15], where a sample size of *n* = 15 per group (total *N* = 45) was determined based on clinical observation, attrition rate and power analysis. Clinical observation suggested that there is moderate to high inter-subject variability with respect to pain, disability and function (patient’s perception). A drop-out rate of 20 % is assumed due to a long intervention period, increase or resolution of symptoms during the intervention, or a need for surgery requiring exit from the study. Power analysis was based on an alpha level of 0.05 and beta of 0.8 resulting in the proposed sample size of 45 [38].

Based on this reported sample size with the same main outcome and design, an *à priori* calculation of the total sample size was performed leading to a group sample of *n* = 20 (total *N* = 60) according to the following assumptions (Software: G*Power3, [68, 69]: test family = F-tests, statistical test = repeated measures ANOVA, effect size = 0.2 (medium), alpha = 0.05, power = 0.82, number of groups = 3, number of measurements = 3, correlation among the repeated measures = 0.5, nonsphericity correction epsilon = 1 and dropouts *n* = 6).

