Evaluations of neuromuscular function are very rare. A study investigating neuromuscular activity of the tibialis posterior muscle reports enhanced activity in flat-arched asymptomatic people during stance [29]. Tibialis posterior and peroneus longus muscle activity with the use of foot orthoses in flat-arched people changed [30], which is in contrast to O’Connor et al. who report that the tibialis posterior showed (at least in running motion) inconclusive activation patterns and no changes between different shoe conditions [31]. Another study showed reduced peroneus, lateral and medial gastrocnemius, and soleus muscle activity during early stance but enhanced tibialis anterior muscle activity in participants with asymptomatic flatfoot but with a history of musculoskeletal pain compared to controls [32]. This underlines the importance of readily available neuromuscular parameters describing gait function [33–35].

Some recent studies present sophisticated measurement approaches of dynamic foot function in pes planovalgus but to the authors’ knowledge, no study to date has evaluated dynamic foot function in patients suffering from acute complaints. Most studies use healthy controls or asymptomatic flatfooted subjects [36, 23, 37]. This makes it difficult to draw clear conclusions with regard to patients.

The aims of this study are therefore to: (i) analyse the efficacy of three different non-surgical therapy regimens in PTTD patients, and (ii) evaluate descriptively functional outcome with a comprehensive biomechanical measurement approach to learn more about functional changes in movement generation and its possible plasticity throughout the intervention.

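### The primary endpoint is set at 12 weeks, but the stated primary test is a three-visit ANOVA in which no term is a week-12 comparison

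*Protocol article*

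**What the plan says.** In the protocol article, the outcome section on the FFI names the outcome: "The overall (i.e., total) FFI score will be analysed as the primary outcome measure". The Data analysis section gives the test. The score "at measurement points 0, week 6 and week 12 will be analysed by 3x3 Analysis of Variance (ANOVA) with repeated measures", with the purpose of "identifying differences in the FFI across groups (FOO, FOE, FOS) and test sessions". The same paragraph then fixes the time point: "The primary endpoint will be set at 12 weeks". The FFI subscales, which are secondary outcomes, get the same ANOVA.

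The sample size paragraph at the end of that section uses "test family = F-tests, statistical test = repeated measures ANOVA", with effect size f = 0.2, "alpha = 0.05, power = 0.82", three groups, three measurements, correlation 0.5, epsilon 1 and 6 dropouts out of 60. It does not say whether the between-groups, within-subjects or interaction effect was meant. The Background gives the first aim as to "analyse the efficacy of three different non-surgical therapy regimens in PTTD patients".

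**The concern.** A 3x3 repeated-measures ANOVA yields three F tests, and none of them compares the arms at week 12.

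- **Time** (2 df) compares visits and no arms.
- **Group** (2 df) averages the three visits, including week 0, where randomised arms have equal expected means.
- **Group by time** (4 df) asks whether the arms' profiles differ in any way across weeks 0, 6 and 12.

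The interaction is the natural candidate for a treatment effect, but a significant result can come from week 6 alone. The trial could then be reported as positive with no difference at the time point it calls primary. Because the text does not name the deciding term, two analysts could also follow it and base the primary conclusion on different tests.

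**Working it through.** **Inputs, all from the sample size paragraph:** f = 0.2 (f² = 0.04), N = 60 − 6 = 54 analysed (18 per arm if equal), m = 3 visits, ρ = 0.5, ε = 1, alpha 0.05.

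**Step 1. Which term does the stated power belong to?** Noncentral F power for each:

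| Term | λ | df | Power |
|---|---|---|---|
| Group | f²Nm/(1+(m−1)ρ) = 0.04·54·3/2 = 3.24 | 2, 51 | 0.327 |
| Time | f²Nm/(1−ρ) = 0.04·54·3/0.5 = 12.96 | 2, 102 | 0.898 |
| Group × time | 12.96 | 4, 102 | 0.816 |

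Only the interaction matches 0.82, so the trial was sized on the 4-df omnibus term.

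**Step 2. What does that effect imply at week 12?** Let the arm difference follow a time profile t over weeks 0/6/12, with equal baseline means and equal SDs. The interaction f² is the between-arm variance of the profile multiplier (call it g², in SD² units) times var(t), so g² = 0.04/var(t). The between-arm variance at week 12 is g²·t₁₂². Adjusting for baseline leaves residual variance 1 − ρ² = 0.75, so for the week-12 ANCOVA λ = 54·g²·t₁₂²/0.75 with df 2 and 50. The time profile is an assumption, because the article gives none. Interaction power is 0.816 in every row.

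| Profile 0/6/12 | var(t) | g²·t₁₂² | λ | ANCOVA power |
|---|---|---|---|---|
| 0/0.5/1 (linear) | 0.1667 | 0.240 | 17.28 | 0.959 |
| 0/1/1 (complete by week 6) | 0.2222 | 0.180 | 12.96 | 0.888 |
| 0/0/1 (week 12 only) | 0.2222 | 0.180 | 12.96 | 0.888 |
| 0/1/0.85 | 0.1939 | 0.149 | 10.73 | 0.820 |
| 0/1/0.75 | 0.1806 | 0.125 | 8.97 | 0.742 |
| 0/1/0.5 | 0.1667 | 0.060 | 4.32 | 0.422 |
| 0/1/0 (week 6 only) | 0.2222 | 0 | 0 | 0.050 |

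The last row shows the mismatch: the interaction rejects in 82% of trials and the week-12 test at its 5% error rate. Simulation with 20,000 trials gave 0.820 and 0.050 for that row, and 0.0485 and 0.048 when there was no effect.

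**Step 3. A second effect size.** Suppose one arm is 0.8 SD better at week 12 than the other two, so that the between-arm variance is 0.64·2/9 = 0.1422. ANCOVA: λ = 54·0.1422/0.75 = 10.24, power 0.80. The interaction has 0.56 with linear onset (λ = 7.68), but 0.705 with 0/1/1 or 0/0/1 (λ = 10.24). If 0.8 SD is instead a week-6 peak of which 75% remains, the order reverses: ANCOVA 0.54, interaction 0.60.

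**Step 4. Pairwise comparisons after the overall test.** With evenly spaced arms at −a, 0 and +a, 2a²/3 = 0.24 gives a = 0.60 SD, and 2a²/3 = 0.18 gives a = 0.52 SD. The standard error of a pairwise difference is √(0.75·2/18) = 0.289 SD. At 5% on 50 df, adjacent arms have power 0.53 and 0.42. The outer pair (1.20 and 1.04 SD apart) has 0.98 and 0.94.

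**Sensitivity to attrition.** The same section also mentions 20% dropout. With 48 analysed, the interaction has 0.759 and the week-12 ANCOVA 0.934 (linear) or 0.844 (0/1/1 or 0/0/1).

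**The case against.** Repeated-measures ANOVA is a legitimate and conventional analysis, and it agrees with the sizing. In a randomised trial the interaction validly carries the arms' differences in change from baseline, so including week 0 in it is a matter of efficiency. The group main effect does dilute the treatment difference, but the trial was not sized on that term. All of this stands, and the point does not claim that the ANOVA is invalid.

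A false lead from week 6 in its pure form needs an effect that disappears completely while orthoses and exercise continue to week 12. That is an extreme case. It shows what the test responds to; it is not a forecast.

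Two stronger readings are tempting, and the document supports neither.

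- A reader might infer that the arm-versus-arm comparisons and their error control are unplanned. The article names none, but such follow-up tests are commonly left to a full protocol or analysis plan, and neither is shown. Their absence here is not a finding.
- A reader might infer that the ANOVA always wastes power. It does not. The comparison depends on a time course that the article does not give, and once less than about 85% of the week-6 difference remains at week 12, the interaction rejects more often. It then does so partly for a difference that is not the stated endpoint.

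What survives is the mismatch between endpoint and test. Follow-up contrasts held elsewhere would not make the named primary test a week-12 test.

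**Conclusion.** The point holds in this form: the stated primary test does not correspond to the stated 12-week endpoint, and the deciding term is not named. The power statement shows that the sizing rests on the 4-df interaction.

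At the planned effect size, with 18 completers per arm and correlation 0.5, a baseline-adjusted week-12 comparison has 0.96 power with linear onset and 0.89 if the effect is complete by week 6 or appears only at week 12, against 0.82 for the interaction. That is a gain of 7 to 14 points. It rests on equal SDs, equal expected baselines, equal arm sizes and at least about 85% of any week-6 difference remaining at week 12. With 75% remaining the new analysis has 0.74 and is the weaker of the two.

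This should be fixed. It is not a fatal flaw, because the planned ANOVA is valid for the broader question it asks.

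**What to change.** State the primary analysis as total FFI at week 12 compared across the three arms with baseline FFI as covariate. Use either ANCOVA or the week-12 contrast of a mixed model with weeks 6 and 12 as outcomes and baseline as covariate. Test the overall 2-df arm effect at 5%. If it is significant, test FOO against FOS, FOE against FOS and FOE against FOO, each at 5%, with 95% confidence intervals. For three arms this is a closed procedure and holds the familywise error at 5%. If an unseen plan already fixes these contrasts, attach them to this model. Use the same model for the FFI subscales and keep the 3x3 ANOVA and the week-6 results as supportive.

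The cost is wording: FFI at weeks 0, 6 and 12 is already scheduled. There are two downsides to accept openly. Power is lower if the effect wanes after week 6. Pairwise power for adjacent, evenly spaced arms also stays low, at about 0.42 to 0.53, so a non-significant pair should not be read as equivalence.

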### Procedure

After the clinical examination, participants will be forwarded to the study centre for further anamnestic (medical history) pre-tests. A 1st measurement appointment will then be finalised. Meanwhile, fabrication of the foot orthoses takes place. At the 1st measurement appointment, participants’ anthropometrics and static unloaded and loaded foot posture for characterisation will be assessed. Following this, the participants’ foot health status (using the Function Index FFI, German Version (or FFI-D) [41, 42]), functional impairment (using the Pain-Disability-Index PDI [43, 44]), and current pain perception (using a VAS [38]) will be assessed. Biomechanical measurements of standing posture, level walking and walking down stairs will then be taken. After biomechanical testing, a re-evaluation of pain assessment with a VAS will be conducted.

After the 1st measurement appointment, an intervention period will follow for 12 weeks. All participants will receive a guideline for load management during the intervention and an activity diary with accompanying assessments (FFI, PDI and VAS after 6 weeks). After the 12-week intervention period, a 2nd assessment of the patient’s foot health status (FFI), functional impairment (PDI) and current pain perception (VAS pre/post-test), as well as the biomechanical tests will follow. If symptoms persist at the end of this period, participants will be transferred to the initial foot surgery centre for further medical assessment and possible ongoing therapeutic care.

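### The plan expects outcome-related drop-out, yet its primary repeated-measures ANOVA uses only participants with all three FFI scores

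*Protocol article*

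**What the plan says.** All of this is in the protocol article.

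- **Data analysis, sample size.** The account of the N = 45 taken from the predecessor trial assumes 20% drop-out. Besides the length of the intervention, the reasons given are "increase or resolution of symptoms during the intervention, or a need for surgery requiring exit from the study".
- **Data analysis, this trial's own calculation.** It builds on that account, uses "effect size = 0.2 (medium), alpha = 0.05, power = 0.82, number of groups = 3, number of measurements = 3" and "correlation among the repeated measures = 0.5", sets the nonsphericity epsilon to 1, allows for 6 dropouts and arrives at 60 participants, 20 per group.
- **Data analysis, primary analysis.** The FFI total at weeks 0, 6 and 12 goes into a 3×3 "Analysis of Variance (ANOVA) with repeated measures identifying differences in the FFI across groups (FOO, FOE, FOS) and test sessions", run in SPSS, with week 12 as the primary endpoint.
- **Procedure.** Baseline and week-12 FFI belong to the two measurement appointments. The week-6 FFI comes with the diary: participants receive "an activity diary with accompanying assessments (FFI, PDI and VAS after 6 weeks").
- **Biomechanical testing.** The only sentence on missing values concerns cleaning the data spreadsheet. It is not a rule for the analysis.

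**The concern.** Apart from duration, each named reason for leaving is a result of treatment, and the reasons point in opposite directions: recovery on one side, worsening or surgery on the other. If the arms differ in efficacy, they can lose different kinds of patient. An analysis restricted to complete series then compares selected subsets, not the randomised groups, and the FFI contrast can be pulled towards or away from zero.

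The three-visit ANOVA adds a loss unrelated to treatment exit. A participant with baseline and week-12 FFI, which is all the primary endpoint needs, also falls out if the week-6 score is missing.

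**Working it through.** **1. Does the plan count dropouts as lost?** Inputs from Data analysis: f = 0.2, alpha 0.05, k = 3 groups, m = 3 measurements, rho = 0.5, epsilon = 1, 60 randomised, 6 dropouts. For the group × session interaction in the G*Power form:

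- noncentrality = f² × N × m × epsilon / (1 − rho)
- df1 = (k − 1)(m − 1) = 4
- df2 = (N − k)(m − 1)

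| N analysed | Noncentrality | df2 | Power |
|---|---|---|---|
| 54 (60 − 6) | 0.04 × 54 × 3 / 0.5 = 12.96 | 102 | 0.816 |
| 60 (none lost) | 0.04 × 60 × 3 / 0.5 = 14.40 | 114 | 0.861 |
| 48 (20% lost) | 0.04 × 48 × 3 / 0.5 = 11.52 | 90 | 0.759 |

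The stated 0.82 matches N = 54. The other tests at N = 54 do not match: within-subject main effect 0.898, between-group 0.327. The calculation therefore assumes that the 6 dropouts contribute nothing.

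**2. How far could the contrast move?** The documents give no exit pattern, so the following are assumptions: 20 per arm, SD 1 at each visit, all correlations 0.5, a linear course, a true FOE–FOS difference of 1.2 SD at week 12, and exit decided by change from baseline at week 6. The quantity followed is change from baseline to week 12, the contrast that the interaction carries.

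- Variance of week-6 change = 1 + 1 − 2 × 0.5 = 1.
- Covariance of week-6 and week-12 change = 0.5 − 0.5 − 0.5 + 1 = 0.5, so half of any shift in week-6 change carries over to week 12.
- The expected four largest of 20 standard normal values are 1.867, 1.408, 1.131 and 0.921.
- Removing the top 2 shifts the mean of the other 18 by 3.275 / 18 = 0.182. Removing the top 4 shifts the mean of the other 16 by 5.327 / 16 = 0.333.
- With opposite tails leaving the two arms, the contrast moves by 2 × 0.5 × shift, which equals the shift.

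| Exits per arm | Best leave FOE, worst leave FOS | Worst leave FOE, best leave FOS |
|---|---|---|
| 2 (the plan's 6 of 60) | 1.2 − 0.182 = 1.02 SD (−15%) | 1.2 + 0.182 = 1.38 SD (+15%) |
| 4 (20%) | 1.2 − 0.333 = 0.87 SD (−28%) | 1.2 + 0.333 = 1.53 SD (+28%) |

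Simulation of the same set-up agrees to within about 0.01 SD (1.01 and 1.39; 0.87 and 1.53). If the same ranks leave every arm, the shifts cancel and there is about no bias. In the first pattern with 4 exits per arm, an analysis that also uses baseline and week 6 gave 1.19 SD, against 1.20 with no data missing.

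**3. How much hangs on the pattern?**

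- With all correlations equal, the covariance of the week-12 score with week-6 change is 0.5 − 0.5 = 0. The distortion therefore enters through the completers' baselines, and the raw week-12 difference is unaffected in this model. Another correlation structure would share it out differently.
- If exit instead follows the final change itself, with the same cut-offs in both groups and exits from both extremes, a true 0.5 SD becomes 0.32–0.38 SD at 10% exits and 0.23–0.36 SD at 20%. With no true difference, equal exit patterns leave the contrast unbiased.

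**The case against.** Four points can fairly be made against this.

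- **A reader might infer that the plan withdraws patients who recover or worsen.** The documents do not support that. The sentence explains an assumed drop-out rate within the account of the predecessor-based N = 45, and the words about exit may attach only to surgery. Procedure plans the week-12 assessment without excepting recovered patients, and refers participants for further care only if symptoms remain at the end of the 12 weeks.
- **A reader might infer that 20% will be lost, or that the best and worst responders leave as a class.** This trial's own calculation allows for 6 of 60, or 10%, and not all of them need leave for outcome reasons. The 4-per-arm figures are therefore an upper scenario.
- **Deletion is not stated.** It follows from the classical form of the ANOVA and from the power figure. An analysis set, imputation or continued follow-up may be laid out in a document not shown, and silence on those is not a fault here.
- **The direction is unknown.** To say that the bias runs towards zero would be too strong, since the reverse pattern inflates the difference by as much.

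All four stand and limit the wording. What remains is a stated method that fits poorly with attrition the plan itself describes.

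**Conclusion.** The point holds as a risk and a worthwhile improvement, not as a demonstrated bias. Outcome-related drop-out is foreseen, the named ANOVA in its classical form needs three scores per person, and the power statement treats the 6 dropouts as lost.

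At the plan's own attrition, the assumed week-6 exit pattern moves a 1.2 SD contrast by about 15% in either direction; at 20% attrition, by about 28% in either direction. Matching patterns across arms bring this to about zero. These figures rest on sharply selective exit, equal correlations and a large true difference. They illustrate and do not bound the effect: exit driven by the final change itself dilutes a smaller difference by proportionally more. How many participants would miss only the week-6 score cannot be estimated from the document.

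**What to change.** 1. Replace the complete-case ANOVA for the FFI total with a likelihood-based mixed model for repeated measures: group × visit, baseline FFI in the model, and the week-12 group contrast as the primary result. Include all randomised participants as allocated and use every available FFI score.
2. State that the week-6 and week-12 FFI will be sought by post or telephone from participants who stop treatment or miss the laboratory visit. This concerns data collection only and leaves clinical decisions as they are.

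**Cost.** One analysis paragraph, plus a mailed form or call for roughly 6 participants (12 at 20% attrition). All groups are already telephoned at weeks 1, 4 and 8, and SPSS fits mixed models. If week-12 FFI were complete for all 60, the plan's own formula would give power of 0.86.

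**Downsides.** Some week-12 scores will follow other treatment. The model protects only if exit depends on data already observed; a participant with no FFI after baseline is not rescued, which is why the second step matters as much as the first.
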